### Intervention

2.6

For patients undergoing posterior lumbar spine surgery under general anesthesia, a researcher will assess whether the patient meets this study’s inclusion and exclusion criteria 1 day before the surgery. The participants who meet the inclusion criteria must sign an informed consent form after being fully informed of the study procedures, potential benefits, and risks. Preoperatively, the NLR will be calculated by dividing the neutrophil count by the lymphocyte count. The pre-calculated NLR threshold of 2 will be accepted. Patients with a preoperative NLR < 2 will be included in Group A (*n* = 110); those with a preoperative NLR > 2 will be included in Group B (*n* = 110). Using a random number table, Group A will be divided into ESPB (EA group, *n* = 55) and control groups (CA group, *n* = 55); Group B will be divided into ESPB (EB group, *n* = 55) and control groups (CB group, *n* = 55). The researcher will allocate the drugs using an envelope method to conceal the randomization sequence; a specially trained anesthesia nurse will deliver the implementation plan to the corresponding operating room before surgery.

ESPB Group (EA group + EB group): Routine anesthesia induction, followed by ultrasound-guided bilateral ESPB with 0.5% ropivacaine (20 mL) after anesthesia induction.Control Group (CA group + CB group): Routine anesthesia induction, followed by ultrasound-guided bilateral ESPB injection with 0.9% saline (20 mL) after anesthesia induction.

Upon entering the operating room, standard intravenous access will be established; noninvasive blood pressure, electrocardiogram, and oxygen saturation (SpO_2_) will be monitored. Considering that most patients undergoing this surgery are older and positioned prone, radial artery catheterization will be performed using the FloTrac sensor to enable invasive blood pressure monitoring and ensure patient safety. All patients will receive total intravenous anesthesia.

With the patient in the supine position, a face mask will be used for oxygenation and denitrogenation for 3 min before anesthesia induction. Anesthesia induction will include midazolam (0.02 mg/kg), sufentanil (0.2–0.3 μg/kg), propofol (1.5–2 mg/kg), and atracurium (0.6 mg/kg). After the disappearance of the eyelash reflex and jaw relaxation, tracheal intubation will be performed using a visual laryngoscope, and the endotracheal tube will be secured. Mechanical ventilation will be initiated by adjusting respiratory parameters.

After positioning the patient in the prone position, the appropriate lumbar vertebral level will be identified based on preoperative surgical markings using either surface landmarks or ultrasound. The ESPB will be performed bilaterally under ultrasound guidance based on the planned surgical levels. For single-level lumbar surgery (e.g., L3–L4), the block is administered at the transverse process of the upper vertebra (e.g., L3). For two-level surgery (e.g., L3–L5), the block is performed at the middle level (e.g., L4) to ensure optimal spread of local anesthetic. The skin at the puncture site will be disinfected with iodine. An ultrasound low-frequency convex array probe with a sterile sheath will be placed in the parasagittal direction, 3 cm lateral to the midline. The lumbar transverse process, overlying erector spinae, and latissimus dorsi muscles will also be identified. The needle will be advanced in-plane; upon contact with the bony transverse process, confirmation of the correct needle position will be obtained by aspirating 2–3 mL of isotonic saline for hydrodissection. In both EA and EB groups, 20 mL of 0.5% ropivacaine will be administered on each side for the lumbar transverse process surface, providing bilateral ESPB. In the CA and CB groups, 20 mL of 0.9% saline will be administered on each side under ultrasound guidance to the lumbar transverse process surface, serving as a control.

Anesthesia maintenance will utilize propofol (4–6 mg/kg/h) and remifentanil (12–20 μg/kg/h), targeting a BIS range of 40–60. Blood pressure and heart rate will be maintained within 20% of the preoperative baseline values, with adjustments made according to surgical needs. Atracurium will be added intermittently to maintain muscle relaxation. Ten minutes before the end of the surgery, the infusion of anesthetic drugs will be stopped; nonsteroidal anti-inflammatory drugs will not be administered to any patient before the incision or at the end of the surgery. If blood pressure and heart rate variations exceed 20% of the preoperative values, the corresponding medications (5 mg ephedrine, 0.2 mg atropine, 20 mg esmolol, or 0.5 mg nitroglycerin) will be administered promptly. Considering that glucocorticosteroids, such as dexamethasone, may affect the NLR values, they were not considered preoperatively or postoperatively (16).

All patients will receive a standardized 48-h postoperative patient-controlled intravenous analgesia (PCIA) regimen to ensure consistency in analgesic management and allow for objective assessment of analgesic efficacy and opioid consumption. The PCIA formulation will consist of 2 μg/kg sufentanil, 16 mg ondansetron, and 0.9% saline to a total volume of 100 mL. The PCIA device will have a background infusion rate of 2 mL/h, a bolus dose of 2 mL, and a lockout interval of 15 min with no background dose. The patients will be transferred to the PACU for postoperative recovery. If the Visual Analogue Scale (VAS) score at rest is ≥4, the patient or nurse anesthetist will press the PCIA button to administer the drug until the VAS score is <4. If the VAS score remains >4 after three consecutive presses (15 min between presses), the PCIA pump may be gradually adjusted upward in a single dose on demand until the patient’s VAS score is <4. After the pain episodes finish, the PCIA settings will be readjusted to the original parameters. Pain assessments will be conducted every 6 h. Postoperative follow-up data will be collected by designated personnel.

### Data collection and management

2.7

Demographic and clinical data will be collected from all patients, including age, sex, height, weight, body mass index, ASA classification, surgery duration, the intraoperative consumption of drugs, such as propofol and remifentanil, and total analgesic consumption in the first and second 24-h periods postoperatively. Nausea, vomiting, and antiemetic requirements will be recorded in the PACU for the first and second 24-h periods postoperatively. The VAS scores will be recorded at rest and during movement at 2, 4, 6, 8, 12, 24, and 48 h postoperatively. The time of the first pressing of the analgesic pump will be documented. The rescue analgesia rate and analgesic satisfaction scores will be assessed at 24 and 48 h postoperatively. Postoperative satisfaction will be evaluated (0 = dissatisfied, 1 = average, 2 = satisfied, and 3 = very satisfied). Postoperative awakening and extubation time will be recorded. The extubation criteria are that the patient resumes spontaneous breathing with a tidal volume ≥7 mL/kg, demonstrates swallowing reflex, and can follow instructions, maintaining SpO_2_ above 90%. The duration of the postoperative PACU stay and discharge time will be recorded. The occurrence rates of opioid-related side effects will be recorded, including dizziness and urinary retention. The serum NET levels will be measured. In this study, we will assess NETs levels indirectly by quantifying cell-free double-stranded DNA (cf-dsDNA) in serum using the PicoGreen dsDNA quantitation method. Serum samples (5 mL) are collected, centrifuged, and stored at −20 °C. The working dye solution is prepared by diluting PicoGreen reagent 1:200 in TE buffer. A standard curve is constructed using serial dilutions of calf thymus DNA. Equal volumes of diluted sample and dye are mixed and incubated in the dark at room temperature for 5 min. Fluorescence intensity is measured using a fluorescence microplate reader, and the cf-dsDNA concentration (ng/mL) is calculated using the standard curve. This measurement serves as an indirect indicator of NET formation in the postoperative period.

Throughout the study, data will be gathered and managed securely and privately. Data will be collected automatically via the anesthetic information system and vital sign monitoring system. A nursing anesthetist will also collect some data manually. Participants will be identified throughout the study using code numbers rather than names unless otherwise specified. All relevant records and files will be archived for 5 years. During the study, the data will be accessible only to researchers who have signed confidential disclosure agreements and institutional or government auditors. Data without patient identification will be accessible to the general public after the study concludes.

### Outcomes measures

2.8

#### Primary outcome measure

2.8.1

The primary outcomes include nausea and vomiting, antiemetic requirements in the PACU, and the first and second 24-h periods postoperatively, and include the neutrophil count, lymphocyte count, and NLR on the first postoperative day. Patients with a nausea and vomiting score ≥1 (0 = no nausea, 1 = nausea, 2 = retching, 3 = vomiting) will be treated with ondansetron as an antiemetic. Please refer to the attached nausea and vomiting scoring sheets.

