**Overview:**

This prospective, double-blind, single-center, parallel-group study will enroll 220 patients undergoing elective lumbar spine surgery under general anesthesia. Patients will be stratified by a preoperative NLR threshold of 2 into two equal groups and further randomized to receive either ultrasound-guided ESPB with ropivacaine or a saline control after anesthesia induction. All participants will receive standard PONV prophylaxis with intravenous ondansetron. Primary endpoints include the incidence of nausea, vomiting, and antiemetic requirements in the first and second 24-hour postoperative periods, as well as postoperative NLR. Secondary endpoints include pain scores, intraoperative anesthetic consumption, total postoperative analgesic use, time to first analgesic pump activation, patient satisfaction, recovery times, length of stay, opioid-related side effects, and serum neutrophil extracellular traps.

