### Sample size calculation

2.11

To calculate the sample size for the primary research objective, use the “Tests for Two Ordered Categorical Variables” module in PASS software. Set the test power to 1 − β = 0.8 and significance level *α* = 0.05; use a 1:1 ratio between the NLR < 2 and NLR ≥ 2 groups. For the NLR < 2 group, the composition ratios of the PONV states considered as no, nausea, retching, and vomiting are 0.575, 0.050, 0.001, and 0.375, respectively. For the NLR ≥ 2 group, the composition ratios for PONV no, nausea, retching, and vomiting are 0.250, 0.100, 0.050, and 0.600, respectively. The calculated sample size is 94 cases, considering a 10% dropout rate. The final sample size is 106, with 53 patients in each group.

Use the “Tests for Two Proportions” module in PASS software to calculate the sample size for one of the secondary objectives: determining whether preoperative NLR can serve as a biomarker for PONV. Set the test power to 1 − β = 0.8 and significance level to *α* = 0.05; use a 1:1 ratio between the control and thoracic paravertebral nerve block groups. Nausea and vomiting rates are 8.3 and 33.3%, respectively. The calculated sample size is 82, considering a 10% dropout rate. The final sample size is 92, with 46 patients in each group.

The baseline NLR levels are first divided into two strata, and randomization is performed within each stratum. The sample size of each group in this study is 55.

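### Section 2.8.1 names about nine unranked and partly redundant primary outcomes, the Abstract gives a different list, and the sample size covers only PONV with no time window, so no single endpoint carries the trial's primary claim.

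*Protocol article*

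**What the plan says.** Section 2.8.1 (Primary outcome measure) gives the clinical part of the list: "The primary outcomes include nausea and vomiting, antiemetic requirements in the PACU, and the first and second 24-h periods postoperatively". The laboratory part follows in the same sentence: the outcomes also "include the neutrophil count, lymphocyte count, and NLR on the first postoperative day". The same section links the score to treatment: "Patients with a nausea and vomiting score ≥1 (0 = no nausea, 1 = nausea, 2 = retching, 3 = vomiting) will be treated with ondansetron".

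The Abstract (Overview) has a different list: "Primary endpoints include the incidence of nausea, vomiting, and antiemetic requirements in the first and second 24-hour postoperative periods, as well as postoperative NLR". It has no PACU window and no separate neutrophil or lymphocyte count.

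Section 1.1 makes the effect of ESPB on both NLR and PONV the primary objective.

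Section 2.11 contains two sample-size calculations, each for one PONV outcome at power 0.8 and a significance level of 0.05. The first uses a four-level score, where for NLR < 2 "the composition ratios of the PONV states considered as no, nausea, retching, and vomiting are 0.575, 0.050, 0.001, and 0.375". The second uses a nausea-and-vomiting proportion, 8.3% against 33.3%. Neither names a time window, and there is no calculation for NLR.

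Section 2.13 assigns a test to each type of variable. It states no test level and does not rank the outcomes.

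**The concern.** Choosing the primary outcome is a protocol decision. Here the choice is a list with no leading member and no rule for success. A favourable result in any one window or component could be reported as a positive primary finding, and a reader could not tell which result the trial was built to test.

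Three features make the list harder to interpret:

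- The PACU stay lies within the first 24 h, so those two windows overlap.
- Under the score-≥1 treatment rule, yes/no antiemetic use should match yes/no PONV in the same window.
- NLR is the quotient of the two counts listed beside it (section 2.3).

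The Abstract and section 2.8.1 also disagree on what is primary, and the power statement is not tied to any one listed endpoint.

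**Working it through.** **1. The plan's own figures.** Both sample sizes reproduce with a two-sided 0.05 and power 0.80, so (1.960 + 0.842)² = 7.849.

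- Ordinal score, tie-adjusted Wilcoxon: N = 7.849 × (1 − Σp̄³) / [12 × 0.25 × (P − 0.5)²]. The mean proportions p̄ are 0.4125, 0.075, 0.0255 and 0.4875, so 1 − Σp̄³ = 0.8135. P = 0.575 × 0.875 + 0.050 × 0.700 + 0.001 × 0.625 + 0.375 × 0.300 = 0.651. This gives N = 93.04, so 94 as stated. With 10% dropout, 47/0.9 = 52.2, so 53 per group and 106 in all, as stated.
- Proportions 0.083 and 0.333, pooled test without continuity correction: 41 per arm, so 82 as stated. With dropout, 82/0.9 = 91.1, so 92 as stated.

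Each figure rests on one PONV test at 0.05. Antiemetic use and the blood measures are not covered.

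**2. Counting section 2.8.1.** The three windows are read as applying to both clinical outcomes.

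| Outcome | Number |
|---|---|
| PONV in PACU, 0–24 h, 24–48 h | 3 |
| Antiemetic requirement in the same windows | 3 |
| Neutrophils, lymphocytes, NLR on day 1 | 3 |
| Total | 9 |

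The single 0–3 score in 2.8.1 and 2.11 supports nine. Counting nausea and vomiting separately adds three, giving 12. The Abstract's list gives 2 + 2 + 1 = 5, or 7 with that split.

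**3. Family-wise error if each outcome is tested at 0.05.** This takes one ESPB-versus-control comparison, no true effect on any outcome, and no adjustment. For independent tests the error is 1 − 0.95^k:

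- k = 12: 46.0%
- k = 9: 37.0%
- k = 6 (the yes/no antiemetic duplicates dropped): 26.5%
- Abstract list, k = 5 or 7: 22.6% or 30.2%

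For two-sided tests on jointly normal statistics, independence is the worst case, so these are ceilings for each count.

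**4. Allowing for correlation.** The documents give no correlations, so a range is assumed. Normal test statistics were simulated with correlation 0.3–0.9 within the PONV block, 0.3–0.7 within the blood block and 0.1 between blocks:

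- 12 outcomes: about 22–42%
- 9 outcomes: about 20–34%
- 6 outcomes: about 18–25%

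With one common correlation of 0.3, 0.5 or 0.7 across all outcomes, the figures are 40%, 32% and 23% for twelve and 33%, 27% and 20% for nine. At a common correlation of 0.9 they fall to about 13% and 12%, but that would require PONV and blood counts to move almost together.

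**The case against.** The strongest defence is that the statistical analysis plan is not shown. A multiplicity adjustment commonly sits there, so its absence from the article is no finding. That stands. The level 0.05 appears only in section 2.11, for sample size, and a reader might infer that every primary outcome will be tested at 0.05. The documents do not say so, and the error rates above are therefore conditional.

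Four further limits also stand:

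- A reader might infer that a false-positive primary result is likely. No scenario here reaches 50%.
- A reader might infer that overlap and duplication inflate the error. They lower it, because duplicated tests are not extra chances. Their harm is to the clarity of the claim.
- Antiemetic use matches PONV only as yes/no outcomes, and only if staff follow the rule. It is not fixed to equal the ordinal score, and the number or dose of antiemetics could carry further information.
- Testing every outcome separately in both NLR strata would double the count, but the documents do not state that this will be done.

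What the defence does not reach is the list itself. An analysis plan can divide alpha among primaries, but the published protocol would still give two different primary lists and a power calculation with no window.

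**Conclusion.** The point holds as a defect in how the protocol fixes its primary outcome. Section 2.8.1 makes about nine outcomes co-equal primaries, ranks none and gives no success rule. The Abstract contradicts it, and section 2.11 powers only PONV, on two scales and with no window.

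If the outcomes were tested unadjusted at 0.05, the family-wise error for one comparison would be about 20–40% rather than 5%. It would be at most 37% for nine outcomes, 46% for twelve, and 26.5% for six once the duplicates are removed. This rests on the assumed test level, the assumed correlations and no true effect on any outcome. The need to name a lead endpoint and reconcile the lists does not depend on those assumptions. It should be settled before unblinding.

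**What to change.** 1. Name one lead primary PONV endpoint, with one scale and one window, compared between ESPB and control. One example is any PONV (score ≥1) from PACU arrival to 24 h. The sponsor may prefer another window or the ordinal score.
2. Because section 1.1 also places NLR in the primary objective, test day-1 NLR second: in a fixed sequence at full alpha, only if PONV is significant, or by Holm across the two.
3. Move the other windows, antiemetic use, neutrophil count and lymphocyte count to secondary.
4. Align the Abstract, 2.8.1 and 2.11, and state in 2.11 the scale, window and comparison to which the power applies. At present 2.11 sizes the primary objective on NLR < 2 against NLR ≥ 2, whereas 1.1 makes the ESPB effect primary.

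The cost is a wording amendment and fewer outcomes that can be claimed as primary. The Abstract reports that recruitment is ongoing with no results, and section 2.12 places unblinding after the trial ends, so there is time.

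The fixed sequence costs PONV no power, but NLR can then be claimed only if PONV succeeds. Under Holm, the worst case tests PONV at 0.025. As an illustration, take a control rate of (0.425 + 0.750)/2 = 58.75%, from the ordinal distributions in 2.11, and an assumed 20-point reduction to 38.75%. With 110 × 0.9 = 99 per arm, power falls from about 81% to 72%. The 20-point reduction is not in the documents.

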#### Secondary outcome measure

2.8.2

The secondary outcomes include the following variables: (1) VAS scores during rest and movement for patients at 2, 6, 12, 24, and 48 h postoperatively; (2) consumption of propofol, remifentanil, and other drugs during surgery, as well as the total consumption of analgesics in the first and second 24-h periods postoperatively; (3) the time of the first press on the patient-controlled analgesia pump, pain satisfaction scores at 24 and 48 h, postoperative recovery time, extubation time, PACU stay time, and postoperative discharge time; (4) the occurrence of opioid-related side effects such as dizziness and urinary retention; (5) the concentration of NETs in serum on the first postoperative day.

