### Statistical analysis

2.13

All data will be statistically analyzed using SPSS software (version 25.0). Continuous variables such as VAS scores will be represented by the mean ± standard deviation if they follow a normal distribution. An independent sample t-test will be employed to compare intergroup differences. If the data do not conform to a normal distribution, the Wilcoxon rank-sum test will be used to compare groups.

For categorical variables, such as sex, the chi-squared or Fisher’s exact test will be used to assess intergroup differences. For ordinal data, such as the degree of vomiting, the Wilcoxon rank-sum test will be used for between-group comparisons.

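### Time to first PCIA press can be censored at 48 h, but the only tests that fit it are a t-test or Wilcoxon, with no rule for patients who never press

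*Protocol article*

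**What the plan says.** Section 2.8.2 names "the time of the first press on the patient-controlled analgesia pump" among the secondary outcomes. On collection, section 2.7 says only: "The time of the first pressing of the analgesic pump will be documented". Table 1 follows the first press from the PACU to 48 h.

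Section 2.6 fixes a common window: "All patients will receive a standardized 48-h postoperative patient-controlled intravenous analgesia (PCIA) regimen". It prompts a press when resting VAS is 4 or more, in which case "the patient or nurse anesthetist will press the PCIA button to administer the drug until the VAS score is <4". It also describes the pump as having "a background infusion rate of 2 mL/h, a bolus dose of 2 mL, and a lockout interval of 15 min with no background dose".

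Section 2.13 sorts variables into continuous, categorical and ordinal. For continuous variables that are normally distributed, "An independent sample t-test will be employed to compare intergroup differences"; otherwise, "the Wilcoxon rank-sum test will be used to compare groups". VAS is the only continuous example named. Time to first press is not mentioned, nor is any time-to-event method, and no value or rank is given for a patient without a press.

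**The concern.** Time to first press is a duration observed within a fixed window. A patient with no press by 48 h does not have a missing value in the usual sense: the time is known to exceed 48 h, which is the best result on this outcome. A t-test or Wilcoxon test needs a value for each patient. If the field is left blank, that patient contributes nothing to either test.

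The comparison is then among pressers only. Pressing happens after randomisation and is something the block is meant to change, so the two sets of pressers are no longer the randomised groups. If ESPB keeps some patients from pressing at all, more good results are removed from the ESPB arm and the difference shrinks. The analgesic effect of ESPB is among the secondary objectives in section 1.1, and this outcome bears directly on it.

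**Working it through.** **Plan's own figure.** There is none to reproduce. Section 2.11 sizes the trial on PONV and gives no power, event count or effect for time to first press.

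**Inputs from the article.** Window 48 h (2.6). 55 patients per cell (2.11), so 55 + 55 = 110 ESPB against 110 control over both NLR strata. Alpha 0.05 (2.11), taken as two-sided because the side is not stated.

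**Assumed input.** The share with no press by 48 h is not given. The range used is 1-10% for control and 5-25% for ESPB.

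**Method.** 1,500 simulated trials per scenario, all patients evaluable, unstratified tests. Four analyses were compared: t-test on pressers only, Wilcoxon on pressers only, Wilcoxon with never-pressers tied at 48 h, and log-rank with censoring at 48 h. The simulation standard error is at most √(0.25/1500) = 0.013.

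**Case 1: the block delays pressing.** Times are exponential. A never-press share p at 48 h fixes the mean at 48/(−ln p) and the median at 48 × ln 2/(−ln p). For p = 0.10 the median is 33.27/2.303 = 14.4 h; for p = 0.25 it is 33.27/1.386 = 24.0 h.

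| Never press, control / ESPB | t-test, pressers | Wilcoxon, pressers | Wilcoxon, tied at 48 h | Log-rank |
|---|---|---|---|---|
| 1% / 5% | 0.72 | 0.65 | 0.79 | 0.88 |
| 2% / 10% | 0.77 | 0.71 | 0.92 | 0.96 |
| 5% / 15% | 0.49 | 0.46 | 0.83 | 0.90 |
| 10% / 25% | 0.38 | 0.37 | 0.89 | 0.93 |

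The estimate shrinks as well. From the median formula, the true differences for the four rows are 11.1 − 7.2 = 3.9 h, 14.4 − 8.5 = 5.9 h, 17.5 − 11.1 = 6.4 h and 24.0 − 14.4 = 9.6 h. Among pressers only, the average simulated median differences were 3.2, 4.2, 3.7 and 3.9 h.

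**Case 2: the block changes only whether a patient presses.** Timing among pressers is the same in both arms (median 6 h).

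| Never press, control / ESPB | t-test, pressers | Wilcoxon, pressers | Wilcoxon, tied at 48 h | Log-rank |
|---|---|---|---|---|
| 2% / 10% | 0.05 | 0.05 | 0.18 | 0.43 |
| 5% / 15% | 0.06 | 0.05 | 0.25 | 0.52 |
| 10% / 25% | 0.04 | 0.04 | 0.52 | 0.76 |

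Here the pressers-only tests stay at about their error rate and cannot see the effect.

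**No difference between arms.** With equal shares (2% / 2% in case 1, 10% / 10% in case 2) all four methods rejected in 0.04 to 0.06 of trials.

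**Within one NLR stratum (55 v 55), case 1.** Pressers-only tests 0.20-0.50, tied Wilcoxon 0.50-0.67, log-rank 0.60-0.77. The ordering is the same.

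**The case against.** A reader might infer that the plan excludes never-pressers. It does not say so. No section limits the comparison to observed times. The reference to all data at the start of 2.13 concerns the software, not the choice of test, and the continuous-variable rule is generic.

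The named Wilcoxon test can also keep everyone. With one 48-h window, never-pressers can be tied at the top rank. In case 1 this costs 4 to 9 percentage points of power against log-rank, so most of the gap in the first table comes from exclusion and not from Wilcoxon itself. The t-test is conditional too: clearly skewed times would be sent to Wilcoxon.

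A reader might also infer that presses occur only at VAS 4 or more, and hence that many patients never press. Section 2.6 prompts a press at that score but does not forbid others, and the nurse anesthetist may press as well. The share could be small. It also depends on the background infusion, on which 2.6 contradicts itself.

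Finally, this is a condensed article, and a censoring rule is often left to a statistical analysis plan that is not shown.

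All of this limits the point, but two things stand. The article does fix a set of tests, and a duration fits only the continuous route, whose first choice is a t-test. That test must either drop never-pressers or give them an arbitrary value. And under either test nothing prevents a blank time from removing the patient.

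**Conclusion.** The point holds as a gap in the stated rule: the tests that fit this outcome take no account of censoring at 48 h, and no rule keeps patients who never press. It does not hold as a claim that the plan drops them.

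If they were left out, power in the assumed range would be 0.37-0.77 against 0.88-0.96 for log-rank when the block delays pressing, and about 0.05 against 0.43-0.76 when it only prevents pressing. Tied Wilcoxon gives 0.79-0.92 and 0.18-0.52, so it is a fair substitute in the first case and clearly weaker in the second.

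These figures rest on assumed never-press shares, the assumed shape of the times and full follow-up. At the low end (1% / 5%) the loss is smaller, 0.65-0.72 against 0.88. The point is minor to moderate and concerns one secondary outcome. Sample size and primary outcomes are unaffected.

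**What to change.** In section 2.13, state that time to first press is a time-to-event outcome:

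- measured from a fixed, named time zero, such as PACU arrival or pump start;
- censored at 48 h or at pump removal, whichever comes first;
- summarised by Kaplan-Meier curves and compared by a log-rank test stratified by NLR group, to match the randomisation.

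If Wilcoxon is kept, state that patients with no press are ranked last at 48 h. Do not use the t-test for this outcome. It would also help to say whether a press by the nurse anesthetist counts as the event.

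The two statements on background infusion in section 2.6 must be reconciled, because they affect how many patients never press.

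The statistical change costs a sentence or two. SPSS 25 runs these methods, and no extra patients or visits are needed. The article reports that recruitment is ongoing, so the rule can be set before unblinding.
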